## Abstract

**Background:**

Endoscopic submucosal dissection (ESD) is widely accepted as a local treatment for gastrointestinal tract tumors. As a simplified endoscopic procedure, hybrid ESD (H-ESD) has been performed for colorectal neoplasms in recent times. However, whether H-ESD is superior to conventional ESD (C-ESD) for patients with early gastric neoplasms (EGN) remains unclear. In this trial, we will compare the treatment outcomes of H-ESD and C-ESD. We hypothesize that the procedure time for H-ESD is shorter than that for C-ESD.

**Methods:**

This is an investigator-initiated, multi-center, prospective, randomized, open-label, parallel-group trial to be conducted beginning in August 2020 at nine institutions in Japan. We will determine if H-ESD is superior to C-ESD in terms of procedure time in patients with EGN diagnosed as macroscopically intramucosal (T1a) differentiated carcinoma ≤ 20 mm in diameter without ulcerative findings according to current Japanese gastric cancer treatment guidelines. A total of 82 patients will be recruited and randomly assigned to either the C-ESD or the H-ESD group. The primary outcome is ESD procedure time. Secondary outcomes include mucosal incision, time and speed of submucosal dissection, en bloc resection, complete resection, curability, adverse events related to the ESD procedure, extent of dissection before snaring, volume of injection solution, number and time of hemostasis, thickness of the submucosal layer in the resected specimen, and handover to another operator. The stated sample size was determined based on the primary outcome. According to a previous report comparing the procedure times of C-ESD and H-ESD, we hypothesized that H-ESD would provide a 0.2 reduction in logarithmically concerted procedure time (−37%). We estimated that a total of 82 participants were needed to reach a power of 80% for a *t*-test with a significance level of 0.05 and considering a 10% dropout.

**Discussion:**

This trial will provide high-quality data on the benefits and risks of H-ESD for EGN patients. The results of this study could lead to improved outcomes in patients with EGN undergoing ESD. The results will be presented at national and international meetings and published in peer-reviewed journals.

**Trial registration:**

UMIN-CTR UMIN000041244. Registered on July 29, 2020.

## Background

Endoscopic resection (ER) has become popular as a local treatment for early gastric neoplasms (EGN) without lymph node metastasis. ER is less invasive than surgery and preserves organ function, contributing to maintaining the patient’s quality of life after treatment [1]. Endoscopic mucosal resection (EMR) using an endoscopic steel snare, a simple technique that can be performed quickly, was first developed as an ER technique for EGN [2]. However, snaring for resections of lesions larger than 20 mm or ulcerated lesions presents a technical limitation in that lesions of this size approximately correspond to the diameter of the snare. EMR for such lesions results in a high rate of piecemeal resections, associated with a high local recurrence rate and difficulty in accurate histological assessment [3].

Later, endoscopic submucosal dissection (ESD) using an endoscopic steel knife (endo-knife) was developed for circumferential incision and subsequent submucosal dissection from the proper muscle layer [4]. ESD allows for en bloc resections, even for lesions larger than 20 mm and/or ulcerated lesions, and accurate histological assessments.

According to the current Japanese gastric cancer treatment guidelines, “macroscopically intramucosal (T1a) differentiated carcinoma ≤ 20 mm in diameter without ulcerative findings” is defined as an “absolute indication of EMR or ESD” [5, 6], while lesions larger than 20 mm and/or with ulcerative findings are indicated as an “absolute indication of ESD” or an “expanded indication of ESD” based on the lesion size and presence or absence of ulcerative findings. Previous meta-analyses have suggested that the en bloc resection rate of EMR is significantly lower than that of ESD when gastric lesions exceed 10 mm in size [7–9]; however, previous reports have also suggested that ESD for EGN is more time-consuming and carries a higher risk of perioperative complications due to the requirement of specialized skills needed to perform the procedure [9]. Currently, in clinical practice, considering curability, rather than procedure time and/or risk of complications, ESD is likely to be selected in most cases, even when the gastric lesion meets the absolute indications for EMR or ESD [10].

In this situation, a modified endoscopic procedure called hybrid ESD (H-ESD) has been developed by fusing ESD with EMR. This procedure involves making a circumferential mucosal incision with a subsequent partial submucosal dissection as part of the ESD procedure, followed by snaring, as with EMR. H-ESD is a simplified procedure involving planned snaring during submucosal dissection, and it shows high curability because of the ESD portion of the procedure and a shorter procedural time due to the EMR. Indeed, H-ESD has already been used for colorectal neoplasms, and favorable outcomes with significantly shorter procedure times than with conventional ESD (C-ESD) have been reported [11].

However, the superiority of H-ESD over C-ESD for EGN is still controversial. One retrospective study has shown a significant reduction in procedure time and favorable treatment outcomes with H-ESD, compared with C-ESD [12]. However, another retrospective study failed to show a significantly shorter procedure time for H-ESD [13]. Therefore, it remains unclear whether H-ESD is superior to C-ESD for the treatment of EGN. To address this issue, we aim to conduct a multi-center, randomized controlled trial comparing the clinical outcomes of H-ESD and C-ESD for EGN.

## Methods

### Objective

This study aims to clarify the clinical position of H-ESD for the standard treatment of EGN and compare the treatment efficacies of H-ESD and C-ESD for EGN.

### Trial design

We will conduct a prospective, parallel, randomized, open-label, superiority trial as per the recommendations found in the Standard Protocol Items: Recommendations for Interventional Trials (SPIRIT) checklist [14]. We will report the results in accordance with the Consolidated Standards of Reporting Trials (CONSORT) statement. A flow chart of this study design is shown in Fig. 1. A total of 82 patients with EGN will be recruited and randomly assigned (1:1 ratio) to undergo either H-ESD or C-ESD. The SPIRIT flow diagram is shown in Fig. 2.

**Fig. 1 Fig1:**
[figure not shown]
Schematic of the study design. ESD, endoscopic submucosal dissection

**Fig. 2 Fig2:**
[figure not shown]
SPIRIT flow diagram. H-ESD, hybrid endoscopic submucosal dissection; C-ESD, conventional endoscopic submucosal dissection

### Approvals

This trial has been approved by the Institutional Review Board (IRB) of Kyusyu University for clinical trials (IRB No. 20202005; July 28, 2020) and also by the IRBs of each participating institution. This trial has been registered at UMIN-CRT (ID: 000041244; July 29, 2020). The trial protocol (vol. 1.0; June 1, 2020) was designed in accordance with the SPIRIT guidelines. A SPIRIT checklist is provided in Additional file 1. Attending investigators will obtain informed consent from each patient who volunteers to participate in this study and who meets the eligibility criteria. If any protocol modifications occur, they will be communicated to all study personnel on time.

### Population

#### Inclusion criteria

The inclusion criteria are as follows: (i) age ≥20 years of any sex; (ii) presence of EGN and capable of undergoing ESD as a local treatment; (iii) lesions diagnosed by endoscopic biopsy as gastric adenomas or adenocarcinomas; (iv) lesions endoscopically diagnosed as mucosal lesions ≤20 mm in diameter without ulceration ≤3 months prior to enrollment; (v) Eastern Cooperative Oncology Group Performance Status of 0–2; (vi) capable of listening to oral explanations and reading explanatory documents regarding doctors’ instructions as well as signing consent forms (including the informed consent that will be obtained before enrollment in the trial); and (vi) willingness to comply with all study procedures and be available for the duration of the study.

#### Exclusion criteria

Patients who meet at least one of the following exclusion criteria are considered ineligible for this trial: history of gastric surgery, are currently undergoing dialysis, or requiring continuous administration of heparin during the perioperative period. The concomitant use of other antithrombotic agents will be permitted during the study period. The Japanese guidelines for gastroenterological endoscopy for patients undergoing antithrombotic treatment will be adopted for the management of antithrombotic agents to the enrolled patients [15]. Those with contraindications for endoscopy, ileus, gastrointestinal perforation, or severe respiratory/cardiac disease are also excluded as are patients with metal allergies and those judged to be inappropriate for the study by the attending physician in this trial. Those who do not provide informed consent will also be excluded.

### Recruitment and consent

The patients will be screened by experienced endoscopists in each institution according to the inclusion and exclusion criteria. The endoscopists will assist patients in understanding the benefits and risks of the two treatment procedures, and written informed consent will be obtained from them prior to enrollment.

### Trial intervention

Enrolled patients will be randomized to undergo either H-ESD or C-ESD. Each patient with EGN will be treated using an assigned endoscopic procedure.

### Endoscopists and equipment

Each procedure will be performed at one of the nine institutions by one of the participating endoscopists; each endoscopist in this study has been licensed to practice medicine in Japan for at least 2 years and has performed ≥500 endoscopies. Endoscopists without experience in C-ESD or H-ESD will be required to undergo hands-on training using a pig model before becoming an operator in the study. Handover of the procedure to another operator will be allowed if experienced endoscopists consider the handover clinically desirable for reasons such as prolonged procedure time over 60 min, massive uncontrollable bleeding, or the occurrence of perforation during the procedure. Procedure handover will be done and recorded if the supervisor determines that it is necessary.

Upper gastrointestinal endoscopes (EG-450-RD5, Fujifilm, Tokyo, Japan; GIF-Q260J, Olympus, Tokyo, Japan) attached to a disposable hood (Elastic touch, Top, Tokyo Japan, or D-201-11804, Olympus) will be used in the ESD procedures. A Flush Knife (DK2620J, Fujifilm) or Dual Knife (KD-650, Olympus) will be used in the C-ESD procedure. A SOUTEN (ST1850-20, Kaneka Medix, Tokyo, Japan) will be used in the H-ESD procedure. The SOUTEN is a hybrid knife that combines a needle knife and a snare, where a needle tip is attached to the top of the snare. No regulation is required for the types of injection needles in this study. An electrosurgical unit (ICC200, VIO300, or VIO3, ERBE, Tubingen, Germany) will be used as a high-frequency generator. Sodium hyaluronate solution or sodium alginate solution will be used as a viscous solution for submucosal injections from the injection needle. Normal saline or glycerol will be used for submucosal injections using the endo-knives. Coagrasper (FD-410LR, Olympus), Coagrasper G (FD-412LR, Olympus), RAICHO (RC-1900, Kaneka Medix), RAICHO 2 (RC1550-2, Kaneka Medix), and Hemostat Y (H-S2518, Pentax, Japan) forceps will be used if bleeding cannot be controlled using the endo-knife.

### Endoscopic procedures

C-ESD and H-ESD procedures will be principally performed as en bloc resection. However, if en bloc resection is determined to be too difficult, preventive methods for local recurrence, such as piecemeal resection and additional coagulation using argon plasma coagulation or hot biopsy forceps, will be performed.

Both ESD procedures will be performed under sedation. C-ESD, described in detail elsewhere, consists of marking, injection, mucosal incision, and submucosal dissection [16, 17]. After observing the margin of the lesion, marking dots will be drawn 2–3 mm away from the margin. One of the viscous solutions will be injected into the submucosal layer using an injection needle to lift the target lesion. A circumferential mucosal incision will be made outside the marks. Subsequently, the submucosal layer will be dissected, and the target lesion will be retrieved. Marking, mucosal incision, and submucosal dissection will all be conducted using an endo-knife. There are no regulations for completing a circumferential mucosal incision before or during submucosal dissection in this study. The C-ESD procedure will be switched to traction-assisted ESD (TA-ESD) if the procedure time exceeds 60 min or if it is technically too difficult to ensure appropriate visualization and management of severe perforation or bleeding during C-ESD. However, TA-ESD is not considered a standard treatment because its superiority has not been shown in previous randomized controlled trials (RCTs) [18]. C-ESD can also be switched to H-ESD under the same conditions as those stated above; however, the selection of TA-ESD or H-ESD will depend on the discretion of the attending operator.

The H-ESD procedure will be performed, as described in detail elsewhere, using a SOUTEN high-frequency surgical knife [12, 19]. SOUTEN will be fixed with the snare closed, and only the distal tip will be exposed. Marking, injection, and mucosal incision will be performed in the same manner as described for C-ESD using the tip of the SOUTEN and an injection needle. After completing the circumferential incision, a partial submucosal dissection will be performed using the tip of the SOUTEN. Snaring of the lesion will be performed once the operator considers it possible to perform the resection in an en bloc manner. The open snare will be placed around the lesion, which will subsequently be resected by closing the snare and coagulation. H-ESD can also be switched to C-ESD if the operator considers snaring too difficult to perform. In such cases, the submucosal dissection will be performed until the specimen is retrieved.

Injection of the viscous material can be performed in both C-ESD and H-ESD using an injection needle, but it can also be done in C-ESD using an endo-knife. Hemostasis will be performed in both C-ESD and H-ESD using the tip of the devices if bleeding occurs or if the blood vessels are detected. If bleeding cannot be controlled using only an endo-knife, hemostatic forceps will be used.

Patients will be managed as after regular ESD, including being managed with intravenous nutrition and fasting. Patients will start to receive proton pump inhibitors, including potassium competitive acid blockers after ESD. Enteral diets will start within 2 or 3 days after ESD. If there are no serious adverse events (AEs), patients will be discharged approximately 1 week after ESD. If any AEs occur, investigators will immediately provide appropriate treatment and record it. The endoscopic treatment performed in this study is covered by the current medical insurance, and all costs associated with the study, including the treatment of AEs, will be charged and paid in accordance with the medical insurance system. There is no special compensation system for side effects caused by these treatments.

### Outcome variables

#### Primary outcome

The primary outcome is the procedure time of each ESD among the full-analysis set (FAS). ESD procedure time is defined as the total time from the beginning of the mucosal incision to the completion of the lesion resection, including circumferential mucosal incision, submucosal dissection, snaring, and additional submucosal injections during each procedure.

#### Secondary outcomes

The secondary outcomes are as follows: time of the mucosal incision; time and speed of the submucosal dissection, with or without snaring; en bloc and complete resection, curability, determined by histological assessment of the resected specimen; endoscopic procedural adverse events, including intraoperative perforation, delayed perforation, and delayed bleeding; degree of the dissected submucosal layer before snaring; volume of the injection solution used; number and duration of hemostasis events using a hemostatic device during the procedure; thickness of the submucosal layer in the resected specimen; and whether there was handover to another operator.

### Subgroup analysis

A subgroup analysis will be conducted to investigate the relationship between the procedure time and tumor location, tumor size, operators’ experience, and pathological ulceration. The following four subgroups were defined: tumor location (upper or middle third of the stomach/lower third of the stomach), tumor size (0–9 mm/≥10 mm), operators’ experience with ESD (0–29 cases/≥30 cases), and pathological ulceration (negative/ positive). In the analysis of the subgroups mentioned above, ESD procedure time will be compared between H-ESD and C-ESD as a primary outcome.

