### Statistics

#### Hypotheses and data analysis

The primary efficacy endpoint is the procedure time of the ESD. The null hypothesis is that the procedure time for the H-ESD and C-ESD procedures in patients with EGN is the same.

Analysis of the primary and secondary outcomes will be conducted using the FAS. We plan to analyze complete cases without imputation of missing data because this trial is designed to generate little missing data.

An analysis of covariance for the logarithmically converted ESD procedure time will be conducted with tumor location (upper or middle third of the stomach vs. lower third of the stomach), tumor size (0–9 mm vs. ≥10 mm), and operators’ experience with ESD (0–29 cases vs. ≥30 cases) as covariates. H-ESD will be considered a superior treatment procedure, compared with C-ESD, if the procedure time for H-ESD is significantly shorter than that for C-ESD. A 2-sided *p*-value <0.05 will be considered to indicate statistical significance. In the sub-analysis, if a subgroup factor is one of the covariates, the analysis will be performed without including the sub-group factor as a covariate.

Statistical analyses will be performed by independent statisticians at the Data Center of the Center for Clinical and Translational Research (CCTR) at Kyushu University Hospital. The data will be transferred to SAS statistical software version 9.4 (SAS Institute INC., Cary, NC, USA) for all analyses.

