#### Sample size estimation

In this study, to test the superiority of H-ESD over C-ESD, the sample size was estimated based on the primary endpoint (the logarithmically converted procedure time for ESD). According to a previous report comparing the treatment outcomes of C-ESD and H-ESD, the logarithmically converted procedure times (minutes, mean ± standard deviation (SD)) for C-ESD and H-ESD were 1.578 ± 0.225 and 1.244 ± 0.228, respectively [12]. Considering these results, we hypothesized that H-ESD would provide a 0.2 (37%) reduction in procedure time and estimated the SD of 0.3 conservatively. Based on these assumptions, a total of 74 participants is needed to reach a power of 80% for a *t*-test with a significance level of 0.05. To compensate for a 10% dropout rate, we aim to include 82 participants in the study.

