The conventional EMR technique using snaring, on the other hand, has the limitation of curability. One of the disadvantages of EMR is that the en bloc resection rate is significantly lower than that of C-ESD, especially when the lesions are larger than 10 mm [8, 21, 22]. We expect that this limitation will be compensated for by H-ESD, where snaring is conducted after the circumferential incision and subsequent partial dissection. Therefore, the curability of each procedure will be set as a secondary outcome, and a sub-analysis will be performed on the data from lesions larger than 10 mm.

In the present clinical setting, lesions that fulfill the absolute indication for EMR or ESD are often performed by non-experts since ESD for these lesions is relatively easier than it is for other indicated lesions [5]. This study will, thus, include not only ESD experts but also non-experts, as operator endoscopists, to reflect real-world clinical practices, where the procedures conducted by non-experts are supervised by experts. We will then conduct a sub-analysis stratified by experts and non-experts, which will confirm its usefulness to both operators. Thus, we believe the results obtained from this study in this way will apply to clinical practice.

During the H-ESD procedure, we will use a multifunctional device (the SOUTEN high-frequency surgical knife) that will enable us to perform all procedures other than submucosal injection, including mucosal incision, submucosal dissection, and snaring, with a single device. Since performing ESD using the SOUTEN is much less expensive than it is with other conventional endo-knives, the SOUTEN may contribute to cost savings [19].

In this study, we aim to confirm the superiority of H-ESD over C-ESD for EGN. We expect that our findings will provide valuable information for determining the value of H-ESD for the standard treatment of EGN cases that fulfill the absolute indications for EMR or ESD.

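### The subgroup plan compares the arms separately within each level and promises confirmation for both experts and non-experts, but the trial is sized only for the overall comparison

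*Protocol article*

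**What the plan says.** The Subgroup analysis section defines four factors with two levels each: tumour location, tumour size, operator experience (0-29 versus 30 or more ESD cases) and pathological ulceration. It then states: "In the analysis of the subgroups mentioned above, ESD procedure time will be compared between H-ESD and C-ESD as a primary outcome".

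Hypotheses and data analysis gives the primary model, an ANCOVA of log procedure time with location, size and experience as covariates. For a subgroup factor that is one of these, "the analysis will be performed without including the sub-group factor as a covariate". The significance rule is a two-sided p-"value <0.05 will be considered to indicate statistical significance".

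Sample size estimation covers the overall comparison only: "we hypothesized that H-ESD would provide a 0.2 (37%) reduction in procedure time and estimated the SD of 0.3 conservatively". This leads to 74 evaluable and 82 enrolled patients.

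The Discussion says of operator experience: "We will then conduct a sub-analysis stratified by experts and non-experts, which will confirm its usefulness to both operators".

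**The concern.** Dropping the factor from its own subgroup analysis makes sense only if a separate model is fitted within each level. A model that estimates whether the effect differs between levels must keep the factor's main effect. The method described therefore yields eight within-level comparisons and no direct estimate of a difference between levels.

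That matters most for operator experience, where the Discussion makes a confirmatory promise about each group. Each group contains only part of a sample sized for 80% power overall. If H-ESD saves the same time for experts and non-experts, one group can easily reach significance while the other does not. Such a result could be taken to mean that the technique suits only one kind of operator, although it says nothing of the sort.

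**Working it through.** **Inputs.** From Sample size estimation: difference 0.2 on the log10 scale, SD 0.3, 74 evaluable, 82 enrolled; the earlier report's log10 means 1.578 and 1.244 with SDs 0.225 and 0.228. From the Discussion: a 23% reduction in the other retrospective study. Two-sided 0.05 and 1:1 allocation. *Assumptions:* the expert/non-expert split, which the article does not give; the same effect in both groups; equal arms within a group; no gain in precision from covariates.

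**1. The plan's own figure.** For n per arm, the noncentrality is 0.2 / (0.3 × √(2/n)) on 2n − 2 degrees of freedom. The exact t-test first reaches 80% at n = 37 per arm (power 80.8%), so 74 in total is reproduced. The effect also checks: 1 − 10^(−0.2) = 0.369, the stated 37%.

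**2. Power within an operator group at the planning values.** The same formula is used with the group's n per arm. The two groups contain different patients, so the chance that both are significant is the product of the two powers.

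| Analysed | Split | n per arm in each group | Power per group | Both significant |
|---|---|---|---|---|
| 74 | 50/50 | 18.5 and 18.5 | 50.5% and 50.5% | 25.5% |
| 82 | 50/50 | 20.5 and 20.5 | 54.8% and 54.8% | 30.1% |
| 74 | 75/25 | 27.8 and 9.2 | 68.4% and 27.2% | 18.6% |
| 82 | 75/25 | 30.8 and 10.2 | 73.0% and 29.9% | 21.8% |

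At 74 analysed and an even split, exactly one group is significant in 2 × 0.505 × 0.495 = 50% of trials, although the true effect is the same in both.

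**3. Sensitivity to the article's other figures** (74 analysed, even split). The earlier report's difference is 1.578 − 1.244 = 0.334, and its pooled SD is √((0.225² + 0.228²)/2) = 0.2265. A 23% reduction is −log10(0.77) = 0.114.

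| Difference | SD | Power per group | Both significant |
|---|---|---|---|
| 0.114 | 0.3 | 20% | 4% |
| 0.2 | 0.3 | 50% | 25% |
| 0.2 | 0.2265 | 74% | 55% |
| 0.334 | 0.3 | 91% | 83% |
| 0.334 | 0.2265 | 99% | 98% |

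**4. What an interaction estimate could show.** With four equal cells of N/4 patients, the SE of the difference between the two effects is 0.3 × √(4/18.5) = 0.139 at N = 74. The 95% half-width is 1.994 × 0.139 = 0.28 log10, a factor of 10^0.28 = 1.9. Power is 29% (N = 74) to 32% (N = 82) even if the effect is 0.2 in one group and zero in the other. This half-width belongs to the contrast between groups. The half-width for one group's effect is about 0.20 log10.

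**The case against.** **An unseen analysis plan may contain an interaction test and an exploratory label.** This is fair, and their absence from a condensed article is not the point. The point rests on two things the article does state: the within-level method and the promise to confirm.

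**Dropping the factor is correct within a level, where it is constant.** True. Level-specific models are not invalid and could sit beside an interaction estimate. They simply do not answer whether the effect differs.

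**The planning values are pessimistic.** The article calls SD 0.3 conservative and cites a larger observed difference. Prognostic covariates could add power. A reader might infer that the groups cannot confirm anything; the 4% to 98% range does not support that. It does show that success in both groups depends on an effect or SD more favourable than the one the sponsor chose to plan on.

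**Confirmation is promised for one factor only.** This stands. The Subgroup analysis section speaks of investigating relationships, and nothing in it sets a success rule for each of the eight levels. Nor should the closing words of the first quotation be read as making subgroups co-primary; they most likely name the variable compared.

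**Pathological ulceration.** A reader might infer that "pathological ulceration (negative/ positive") is an invalid subgroup because entry requires lesions "in diameter without ulceration" and the status is read after resection. Entry is judged endoscopically and the subgroup by pathology, so discordant cases are possible and looking at them is coherent. The number of positives is not given. A small stratum is plausible, but removing the factor would be a matter of preference.

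**Size cut.** The Discussion says "a sub-analysis will be performed on the data from lesions larger than" 10 mm, while the subgroup and minimisation use 10 mm or more. The sentence follows a remark on curability and may concern a different analysis. At most this is loose wording.

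**Conclusion.** The point holds in a limited form. The article specifies within-level comparisons and promises confirmation for both operator groups from a sample sized for the overall test alone. At the planned effect, both groups would reach significance in about 25-30% of trials with an even split and 19-22% with a 75/25 split. An even split is the favourable case for succeeding in both. These figures assume a uniform effect and a split that the article does not state; other effects and SDs it cites give 4% to 98%. Confirmation in both groups is therefore unlikely at the planning values, not ruled out. The sample size, the primary ANCOVA and the superiority decision are not affected.

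**What to change.** - **Subgroup analysis, and Hypotheses and data analysis:** for each factor, fit one ANCOVA on the full analysis set with an arm-by-factor term, keeping all three minimisation covariates. Report the H-ESD/C-ESD geometric mean ratio with its 95% confidence interval at each level, and the interaction estimate with its interval. Label all of this exploratory, and say that an interaction interval of about ±0.28 log10 will not settle whether effects differ.
- **Discussion:** replace the promise of confirmation with a statement that the sub-analysis *will estimate the effect in each operator group*.
- **Pathological ulceration:** it may stay as a descriptive subgroup, with a note that the positive stratum may be small because entry requires no endoscopic ulceration.

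No patients or data are added. The cost is that the expert/non-expert statement becomes exploratory. Keeping it confirmatory would need a larger trial: at the planning values, with an even split, 80% power to succeed in both groups takes about 48 per arm per group, or 4 × 48 = 192 evaluable patients.
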